**Fig. 2 Fig2:**
[figure not shown]
Case Report Form

OTN has partnered with Samsung to provide a total of 300 smartphones with the mobile health application pre-loaded. Each device will be connected to the Telus mobile network in addition to having the ability to connect to wireless networks. As all phones need to be distributed as part of the partnership, a targeted sample of 300 patients will be recruited.

#### Allocation

Randomization is centralized, web-based and generated by the Applied Health Research Centre (AHRC) at the Li Ka Shing Knowledge Institute of St. Michael’s Hospital. Randomization is stratified by site using randomly permuted blocks of varying sizes, which are not known by the study team.

Once the participant has been enrolled and the baseline assessments are completed, randomization occurs in REDCap™, a web-based electronic data entry system, where the participant is automatically assigned a group allocation (ITG or WLC).

#### Interventions

##### Mobile Application (E-Health Intervention)

The intervention is a commercially available mobile application that is designed to serve as a virtual coach for patients with T2DM. The application allows participants to enter a range of baseline clinical information, in addition to ongoing data related to diabetes management, including blood glucose values, daily medications, food intake, and activity levels (https://www.bluestardiabetes.com/). The application analyzes inputted data to provide tailored messaging to ‘coach’ participants with respect to their diabetes management. Coaching is a process of continuous improvement involving education regarding targets, negotiating a plan of action to achieve the target, and subsequent monitoring of the patient’s progress toward achievement of the target [18, 19]. Lifestyle coaching empowers participants by giving them the knowledge and skills to work in partnership with providers to achieve health goals [18, 19]. The mobile application has been shown in other contexts and settings to be effective at teaching patients with T2DM about dietary impacts on their blood glucose levels, encouraging patients to generate higher-quality blood glucose data for enhanced self-monitoring, and to improve glycemic control as represented by reduction in levels of HbA1c [20, 21].

The intervention is believed to improve disease control through two patient-mediated processes: tailored messaging and education and facilitated relay of information from the patient to their healthcare provider [22]. The application provides customized, real-time, evidence-based messages based on the Trans-Theoretical Model of Behaviour Change [23] that impact patient motivation, behaviour and education. Educational messages are organized along the American Association of Diabetes Educators 7 Standards of Care [24] and are supported by a library of educational videos that patient can access at any time. The application also facilitates the transfer of disease monitoring data to their primary care provider via a Smart Visit report. The application reminds participants to print this document and bring it to clinical appointments, although the option is available to print the report on demand.

##### Usual Care

Usual care at DEPs are intended to provide multi-disciplinary self-management support to patients with diabetes and may include interactions with a diabetes educator (nurse, nurse practitioner, dietician, pharmacist) or physician specializing in diabetes care. These clinics are designed to support the efforts of the primary care provider, and are not intended to be a substitution for this ongoing relationship. The duration of a patient’s affiliation with a DEP can be highly variable based on clinic, patient and disease factors.

#### Data collection

Baseline information including demographics and health status will be collected using an electronic case report form (CRF) (refer to Fig. 2). HbA1c values will be recorded at baseline, 3 months, and 6 months. Participants who do not have a recent value within two weeks of the study assessment will be given a requisition to perform blood work during the first study visit. Baseline information will be collected by a research assistant via a telephone call, after which the participant will be formally enrolled in the study. Participants who fail to complete the baseline assessment will not be enrolled. Follow up data will be collected using a secure online questionnaire administered via REDCap™ that can be completed by participants from any device with an internet browser and connection (computer, tablet etc.). Weekly reminders will be sent to participants who fail to complete the questionnaire, with a maximum of three reminders. Participants who express a preference for phone communication will be contacted by the research assistant, following the same reminder protocol. Application utilization data is tracked directly through the application and will be extracted at the end of the study.

Healthcare utilization and cost outcome measures will be obtained from health administrative data available through the Institute for Clinical Evaluative Sciences (ICES). At the time of study enrolment, patients will be asked to provide consent to link their OHIP number to health administrative data. ICES is a non-profit research institute with a secure and expansive repository of Ontario’s health-related administrative data from hospital, physician, long term care and other related health services paid for by the provincial health insurance plan. These data are linked using encrypted identifiers. Data from this study will be linked to ICES data using encrypted health card identifiers created by ICES authorized personnel. ICES is a prescribed entity and data custodian under the Personal Health Information Protection Act (PHIPPA).

#### Outcomes

The primary outcome measurement is glucose control, measured by HbA1c at 3 months. Secondary outcomes which will be evaluated at 3 months are patient-reported outcomes measures (PROMs) and patient-reported experience measures (PREMs), which include data on health system utilization using composites of items from: the Commonwealth Fund Survey for Patients with Complex Needs; the Canadian Institutes of Health Research Community Based Primary Health Care Survey; and the EQ5D [25]. Self-efficacy will be measured using two validated scales: the Problem Areas in Diabetes 5 (PAID 5) [26] and the Summary of Diabetes Self-care Activities (SDSCA-6) [27]. All outcomes will be assessed again at 6 months. Intervention usability is an additional secondary outcome which will be evaluated at the end of study as measured by an adapted version of the Mobile App Rating Scale [28] (refer to Fig. 3 for adapted version) and application utilization data collected routinely collected through the application. Utilization measures include the mean number of engagements per week; mean length of time engaging with the application per week; and the frequency of use of each feature per week (e.g., educational tools, Smart Visit Report, blood sugar monitoring).

**Fig. 3 Fig3:**
[figure not shown]
Modified Mobile Application Rating Scale

In this study, costs of healthcare utilization are used to measure resource intensity. Table 1 outlines the databases used to assess these costs, which will be used to determine frequency and intensity of healthcare utilization and overall individual costs using methods developed for use with Ontario data [29]. Costs of health care resource use will be quantified for patients with algorithms developed for patient-level costing using health administrative data and implemented at ICES [29]. Costs for each encounter that generated an encounter-specific payment (e.g., prescriptions, fee-for-service physician visits) are measured as the fee paid for the service. Costs for hospital encounters are determined using the appropriate resource intensity weight for that particular care setting and the weighted cost derived based on Ontario spending. Costs for long-term care are measured as a fixed per diem based on prevailing government payment rates. Emergency department physicians receive substantial alternative payments that are not visit-related, and the algorithms also ascribe those payments, generally on an average per-patient approach. Capitation payments are calculated based on the payment rate and the particular model of primary care for each patient’s physician in each month of the study period. Team-based payments for family health teams and physician bonus payments for pay-for-performance are not ascribed to individual patients and thus are not included in the analysis.

**Table 1 Tab1:** Databases and cost components used in the calculation of health system costs before, during, and after cancer treatment

Database	Description	Cost component
Ontario Health Insurance Plan and (OHIP)	Contains claims paid by OHIP for services provided by all eligible health care providers, including physicians, groups, and laboratories.	• Outpatient physician visits • Laboratory services • Non-physician services
National Ambulatory Care and Reporting System	Contains data from hospital- and community-based ambulatory care services, including day surgery, outpatient clinics, and emergency departments.	• Emergency department visits • Dialysis visits • Oncology clinic visits
Discharge Abstract Database	Contains information on patient separations, notably: • clinical data (diagnoses, procedures) • administrative data (institution information, admission type, length of stay, disposition) • resource consumption, defined using case-mix groups and resource intensity weight	• Inpatient hospitalizations
Client Agency Program Enrolment	Registry of patients enrolled in a primary care model. Data elements include program type (family health team, family health organization, family health network, etc.) and patient enrolment status.	• Capitation costs
Ontario Drug Benefit and (ODB)	Contains claims for prescription drugs covered under the ODB program. Primarily includes drug claims for individuals 65 years of age and older, but also coverage under special ODB programs.	• Medication use
National Rehabilitation and Reporting System	Contains client data from adult inpatient rehabilitation facilities, such as • administrative data (referral, admission, and discharge); • health and functional characteristics; • activities and participation (activities of daily living, communication level, social interaction); and • intervention information.	• Rehabilitation admissions
Continuing Care and Reporting System	Contains information about residents receiving facility-based continuing care services. Range of services includes complex continuing care, extended or chronic care, and residential care providing nursing services (that is, long-term care).	• Complex continuing care admissions and long-term care
Home Care Database	Captures information on all services provided or coordinated by Ontario Community Care Access Centres, including client data, intake and assessment information, admission and discharge, diagnosis and procedures, and care delivery.	• Home care services
Ontario Mental Health and Reporting System	Contains data on patients in adult designated inpatient mental health beds in acute and psychiatric facilities. Data elements include admission and discharge information, diagnoses, service utilization or intervention and procedures.	• Mental health admissions
Assistive Devices Program	Contains data on Ontario residents with long-term disability receiving personalized assisted devices to support basic needs, such as insulin pumps and supplies, home oxygen, and respiratory and ventilator equipment.	• Assistive devices

#### Data analysis

All data will be analyzed according to an intention to treat principle. Patient characteristics and baseline HbA1c levels will be summarized using descriptive statistics, including means, quartiles and standard deviations for continuous variables and proportions for categorical variables. The primary outcome, HbA1c levels between treatment groups, will be analyzed using an analysis of covariance (ANCOVA) with follow-up at three months. PROMs and PREMs will be analyzed using an ANCOVA evaluated at 3 months as well. Continuous secondary outcomes including emergency department visits, physician visits, and hypoglycemic episodes will be analyzed using Poisson regression predicted with the two treatment groups. Ordinal categorical variables including medication adherence and frequency of glucose monitoring will be analyzed using an ordinal regression model for the two treatment groups. We will use regression analyses to separately estimate the difference in healthcare costs between the intervention and control groups and include any covariates that are observed to be different between groups in baseline comparisons. To identify the regression model that fits best with the cost data and potential skew, we will follow the steps suggested by Manning and Mullahy [30] to decide between regression on transformed cost data or generalized linear models.

Six-month follow-up data for the immediate treatment group will be analyzed descriptively. In addition, HbA1c levels will be compared at the 6-month point between the two treatment groups using an ANCOVA which will control for baseline HbA1c levels. Application utilization data will be analyzed descriptively, including time (mean duration of use), general frequency of use (mean uses per week), and frequency of use for each application feature. Subgroup analyses based on site and patient demographics, including age, sex, ethnicity, education, and income [31], will also be conducted. All statistical analyses will be performed using R version 3.0.3 (The R Foundation for Statistical Computing; Vienna, Austria).

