### Setting

Most health services in Ontario, Canada are financed through the publicly-funded Ontario Health Insurance Program (OHIP). OHIP covers medically necessary services provided by physicians, including primary care, emergency services, inpatient medical services, and specialist visits. In addition to OHIP, the Ministry of Health & Long-Term Care funds Diabetes Education Programs (DEPs), which are community-based, multi-disciplinary programs accessible through both physician and self-referral. DEPs provide diabetes education services for clients who are aged 18 or over. Their primary focus is the provision of diabetes education and management services for individuals diagnosed with diabetes or pre-diabetes according to the Canadian Diabetes Association Guidelines [14]. This includes education around self-monitoring blood glucose levels, screening for complications, nutrition, physical activity, and appropriate management strategies including vascular protection, and optimizing glycemic control.

Participating DEPs were selected by the Ontario Telemedicine Network (OTN) and include the Diabetes Health Centre in Thunder Bay, the Diabetes Education Center at North York General Hospital, and two Diabetes Education Centers belonging to the William Osler Health System. OTN reached out to the Provincial Chronic Disease Management-Local Health Integration Leads Council for help in identifying organizations who would be good partners in this initiative. These sites serve a socially and ethnically diverse range of patients with diabetes, representing more than 4500 Ontarians annually. Each site serves distinct populations, including a large aboriginal population in Thunder Bay and visible minorities and new immigrants in the William Osler Health System.

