#### Recruitment

Participants are recruited from participating DEPs associated with three institutions across Ontario. A clinician at each site identifies potential eligible participants during their regularly scheduled clinical appointment. Interested individuals meet with a site coordinator who provides them with an information brochure and a consent form to review. Interested participants contact the research assistant using the dedicated study phone line. The research assistant obtains and documents verbal informed consent and collects baseline outcome measures (refer to Fig. 2, Part A). Participants are then randomized to one of the study arms. Following randomization, the site coordinator collects clinical information (refer to Fig. 2, Part B) and provides participants in the ITG with a study-specific mobile phone. Participants enter initial clinical information into the application (medications, etc.) while in clinic and the data is reviewed for accuracy by a clinician (nurse, nurse practitioner, or certified diabetes educator). Participants in the WLC group receive their application-enabled phone in person following completion of the control phase (three months after enrollment).

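### Randomisation is stratified by site, but no stated analysis model adjusts for site; in the linear models this can make standard errors somewhat too large, with almost no effect on power

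*Protocol article*

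**What the plan says.** Under Allocation, the protocol article states: "Randomization is stratified by site using randomly permuted blocks of varying sizes". Under Setting it adds: "Each site serves distinct populations".

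The Data analysis section of the trial then describes the models:

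- **Primary outcome:** "The primary outcome, HbA1c levels between treatment groups, will be analyzed using an analysis of covariance (ANCOVA) with follow-up at three months". The sentence lists no covariates. The patient-reported outcome and experience measures also get an ANCOVA at 3 months, again with no covariates listed.
- **6-month HbA1c:** compared "using an ANCOVA which will control for baseline HbA1c levels". Nothing else is named.
- **Count outcomes:** these "will be analyzed using Poisson regression predicted with the two treatment groups".
- **Ordinal outcomes:** these "will be analyzed using an ordinal regression model for the two treatment groups".
- **Costs:** regression, adjusting for whichever covariates turn out to differ between the arms at baseline.
- **Site:** mentioned once, as a factor for subgroup analysis.

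The Power calculation section assumes an ANCOVA with a baseline to follow-up correlation of 0.80 and no contribution from site.

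**The concern.** Stratified blocks balance the arms within each site, so differences between sites largely drop out of the treatment contrast. If the model has no site term, those differences stay in the residual variance from which the standard error is computed. The reported standard error then exceeds the true sampling variability of the estimate. Confidence intervals are too wide and the test rejects less often than its nominal 5%. The analysis does not reflect the way patients were randomised.

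The document itself gives some reason to expect site to matter, since it describes the sites' populations as distinct. The cost-model rule adds to the problem. A rule that admits only covariates seen to differ between arms will tend to pass over a factor that the randomisation has balanced, however prognostic that factor is.

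**Working it through.** **Inputs from the Power calculation section:** difference 0.7, SD 2, correlation 0.80, alpha 0.05, N = 300 × 0.85 = 255.

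**Assumptions, not in the document:** 1:1 allocation (127.5 per arm); two-sided alpha; f, the share of post-baseline residual variance due to site, between 0 and 20%.

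**1. The plan's own figure.** Residual SD = 2 × √(1 − 0.80²) = 1.2. SE = 1.2 × √(2/127.5) = 0.1503. Power = Φ(0.7/0.1503 − 1.96) = Φ(2.70) = 0.9965, or 0.9963 with the noncentral t on 252 degrees of freedom. The stated 0.997 reproduces.

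**2. Effect of omitting site in a linear model.** The ratio of the model SE without site to that with site is 1/√(1 − f). The true rejection rate under no effect is then 2 × [1 − Φ(1.96/√(1 − f))].

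| f | SE ratio | Type I error without site, formula | Type I error without site, simulated |
|---|---|---|---|
| 0% | 1.000 | 5.0% | 4.8% |
| 2% | 1.010 | 4.8% | 4.5% |
| 5% | 1.026 | 4.4% | 3.9% |
| 10% | 1.054 | 3.9% | 4.0% |
| 20% | 1.118 | 2.8% | 3.1% |

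The simulation used three sites of 85, 1:1 within site, baseline unrelated to site, and 6,000 trials per setting (Monte Carlo error about √(0.05 × 0.95/6000) = 0.3 percentage point). Under no effect, the mean model SE without site was about 0.1505 at every f. With site it was 0.1466, 0.1428 and 0.1345 at f = 5%, 10% and 20%. The actual spread of the estimates was practically the same under both models (for example 0.1357 for both at f = 20%). So the estimate itself is no less precise; only its reported SE is wrong. With site in the model, type I error was 4.5% to 5.2%.

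**3. Power at the planned 0.7 difference.** The protocol does not say whether its residual SD of 1.2 includes site variation, so both readings are shown.

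| f | 1.2 is total SD: without / with site | 1.2 is within-site SD: without / with site |
|---|---|---|
| 2% | 0.9968 / 0.9970 | 0.9963 / 0.9965 |
| 5% | 0.9972 / 0.9976 | 0.9959 / 0.9965 |
| 10% | 0.9978 / 0.9984 | 0.9952 / 0.9965 |
| 20% | 0.9987 / 0.9994 | 0.9932 / 0.9965 |

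The largest loss is 0.9965 − 0.9932 = 0.0033, about 0.3 percentage point.

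**4. Count and ordinal models.** The derivation in step 2 depends on a residual variance estimated from the data. A plain Poisson model has none: its SE for the log rate ratio depends on the event totals and hardly changes when a balanced site term is added. In ordinal regression, omitting a prognostic factor mainly pulls the treatment coefficient towards zero; it does not inflate the SE.

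**The case against.** The strongest objection is that this is silence, not exclusion. The primary ANCOVA sentence names no covariates, not even baseline HbA1c, although the power calculation clearly relies on it. It is not a full model specification, and a condensed article commonly leaves the covariate list to documents not shown here. This stands for the primary and patient-reported ANCOVAs: a reader might infer that site will deliberately be left out of them, and the text does not say so. It does not dispose of the point. For the 6-month, count and ordinal models the article does state the predictors, and for costs it states a selection rule. Site is in none of them.

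A reader might also infer a material loss of power. Such a loss appears only at a smaller effect. At 0.4 points, for instance, with within-site SD 1.2 and f = 20%, power is Φ(2.66 − 2.19) = 0.68 without site against Φ(2.66 − 1.96) = 0.76 with it. The protocol plans for 0.7, where the loss is negligible.

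A third inference, that SEs are overstated in every model, fails for the Poisson and ordinal models (step 4 of the working).

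Finally, the document gives no between-site variance. Distinct populations need not mean distinct 3-month HbA1c once baseline is adjusted for. The upper end of the range (f = 20%, a between-site SD of 0.6 beside a within-site SD of 1.2) is an assumption.

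**Conclusion.** The point holds as a mismatch between randomisation and stated analysis, of modest size. In the linear models the treatment estimate is unbiased, and any error is conservative: a model SE about 1% to 12% too large for an assumed site share of 2% to 20% of residual variance, and no error if site is not prognostic. Power for the stated 0.7-point difference stays at or above about 0.993. These sizes rest on 1:1 allocation, a two-sided test and the assumed range for f. For the count, ordinal and cost models, the case for including site is consistency with the design, not a demonstrated error in the standard error. This is a nearly free improvement; it does not threaten the trial's conclusions.

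**What to change.** State the primary model in one sentence: 3-month HbA1c on treatment, baseline HbA1c and site, all as fixed effects. Include site likewise in the 6-month HbA1c, patient-reported, count, ordinal and cost models. In the cost model, site should enter regardless of the observed baseline comparison.

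Define site exactly as the randomisation system uses it. Recruitment says "Participants are recruited from participating DEPs associated with three institutions across Ontario", while Setting lists four centres, two of them in one institution. That is not a contradiction, but the reader cannot tell whether the strata number three or four.

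The cost is 2 degrees of freedom for three strata or 3 for four, out of about 250. No extra data are needed, because site is recorded at randomisation. The article reports 14 participants recruited so far, so at that stage the change could be made well before any comparative result. In the ordinal model, the treatment odds ratio would become conditional on site, and the report should say so.

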**Methods:**

The primary objective of this study is to evaluate if a mobile application designed to improve self-management among patients with type 2 diabetes (T2DM) improves glycemic control compared to usual care. The secondary objectives are to determine the effects on patient experience and health system costs; evaluate how and why the intervention worked as observed; and gain insight into considerations for system-wide scale-up. This pragmatic, randomized, wait-list-control trial will recruit adult participants from three Diabetes Education Programs in Ontario, Canada. The primary outcome is glycemic control (measured by HbA1c). Secondary outcomes include patient-reported outcomes and patient-reported experience measures, health system utilization, and intervention usability. The primary outcome will be analyzed using an ANCOVA, with continuous secondary outcomes analyzed using Poisson regression. Direct observations will be conducted of the implementation and application-specific training sessions provided to each site. Semi-structured interviews will be conducted with participants, healthcare providers, organizational leaders, and system stakeholders as part of the embedded process evaluation. Thematic analysis will be applied to the qualitative data in order to describe the relationships between (a) key contextual factors, (b) the mechanisms by which they effect the implementation of the intervention, and (c) the impact on the outcomes of the intervention, according to the principles of Realist Evaluation.

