#### Power calculation

Power was determined assuming an ANCOVA analysis with an estimate correlation between baseline and follow-up HbA1c measurements of 0.80. The power to detect a difference of 0.7 % [32] in HbA1c levels using a standard deviation of 2 % [32] between treatment groups at 3 months is 0.997 with an alpha of 0.05 based on a sample size of 255 (which assumes a dropout rate of 15 % from the target sample size of 300 participants).

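### Three secondary count outcomes are assigned to Poisson regression with no allowance for overdispersion, so their confidence intervals are likely to be too narrow

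*Protocol article*

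**What the plan says.** The Data analysis section of the protocol article gives one sentence to these outcomes: "Continuous secondary outcomes including emergency department visits, physician visits, and hypoglycemic episodes will be analyzed using Poisson regression predicted with the two treatment groups". The abstract says the same in shorter form: "with continuous secondary outcomes analyzed using Poisson regression". Treatment group is the only predictor named. Neither place mentions overdispersion, a scale parameter, robust standard errors or a negative binomial model.

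The same paragraph treats costs differently. It sets out a procedure, introduced by "To identify the regression model that fits best with the cost data and potential skew", for choosing between a transformed outcome and a generalized linear model. No comparable step is given for the visit and episode counts.

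The article reports no mean, variance or event rate for any count outcome. An alpha of 0.05 appears only in the HbA1c power calculation ("with an alpha of 0.05 based on a sample size of 255").

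**The concern.** A Poisson model is adequate if all patients in an arm share one event rate and events occur independently. The article describes a population in which that is unlikely. The entry criteria are deliberately wide, the sites serve different communities, and contact with the education programs varies by clinic, patient and disease. Insulin pumps are an exclusion but insulin treatment is not, so the risk of hypoglycaemia should differ between patients. With treatment group as the only predictor, all this variation stays in the residual and pushes the variance above the mean.

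The estimated rate ratio is not biased by this, but its model-based standard error is too small. A chance difference in visits or hypoglycaemia, in either direction, would then look better established than it is. Health system utilization is a named secondary outcome, so readers will take these intervals at face value.

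**Working it through.** **Inputs from the article.** Analysed sample size 255 ("based on a sample size of 255"), which is 300 × 0.85 ("which assumes a dropout rate of 15" per cent); alpha 0.05; for HbA1c, a difference of 0.7, a standard deviation of 2 and a correlation of 0.80.

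**Assumed.** Two-sided tests, equal allocation (127 or 128 per arm), and every mean count and variance-to-mean ratio (φ) below.

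**1. The plan's own figure.** The only computed figure is the HbA1c power.
- Residual SD = 2 × √(1 − 0.80²) = 1.2
- Standard error = 1.2 × √(2/127.5) = 0.150
- Power = Φ(0.7/0.150 − 1.96) = Φ(2.70) = 0.9965

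This agrees with the stated 0.997. That calculation does not involve the count outcomes.

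**2. How much rate variation produces overdispersion.** If patients' rates have coefficient of variation c, then φ = 1 + mean × c².
- Assumed mean 3, c = 0.41: φ = 1 + 3 × 0.168 = 1.5
- Assumed mean 3, c = 0.58: φ = 1 + 3 × 0.336 = 2.0
- Assumed mean 0.2, c = 1: φ = 1 + 0.2 × 1 = 1.2

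Modest variation matters for a common event. For a rare one, even large variation leaves φ close to 1.

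**3. Error of the model-based Poisson test.** The true standard error is √φ times the model-based one, so the actual two-sided error is 2 × (1 − Φ(1.96/√φ)).

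| φ (assumed) | 1.96/√φ | Actual error at nominal 5% |
|---|---|---|
| 1.0 | 1.96 | 5.0% |
| 1.2 | 1.79 | 7.4% |
| 1.5 | 1.60 | 11.0% |
| 2 | 1.39 | 16.6% |
| 3 | 1.13 | 25.8% |
| 5 | 0.88 | 38.1% |

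**4. Check by simulation.** Counts were generated with no treatment effect for 128 and 127 patients (negative binomial; Poisson at φ = 1), with 20,000 runs per setting. A selection of the settings:

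| Mean | φ | Model-based Poisson | Quasi-Poisson | Robust |
|---|---|---|---|---|
| 0.2 | 1.2 | 6.9% | 4.5% | 4.9% |
| 0.2 | 1.5 | 10.2% | 4.7% | 5.4% |
| 0.2 | 2 | 16.0% | 4.9% | 6.0% |
| 3 | 1.5 | 10.5% | 4.9% | 5.1% |
| 3 | 2 | 16.5% | 5.3% | 5.6% |
| 3 | 3 | 26.0% | 5.2% | 5.5% |
| 3 | 5 | 37.3% | 5.0% | 5.4% |
| 2 | 8 | 48.5% | 5.1% | 6.0% |

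The simulation follows the formula. Over all settings tried (φ from 1 to 8), quasi-Poisson stayed at 4.5% to 5.3% and robust standard errors at 4.9% to 6.0%. Negative binomial regression was not simulated.

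**The case against.** The best defence is that the article names a model and a predictor but not a variance estimator. Poisson regression with robust standard errors is consistent with its sentence, and a full protocol or analysis plan that is not shown could specify it. This stands as a limit: the article does not show that model-based standard errors will be used. It does not remove the point. The model is a stated choice, its default standard errors rest on variance equal to mean, and the authors planned for awkward distributions in costs only.

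A reader might infer that false-positive rates of 10% to 40% are established for all three outcomes. The documents do not support that. The range needs φ between about 1.4 and 5.4, and no dispersion is given. Emergency department visits over three months may be rare and close to nominal, while hypoglycaemic episodes could lie above the range.

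A reader might also infer that repeat events in one patient are enough to cause the problem. They are not: a constant-rate Poisson process also gives repeats, with variance equal to mean. Differences in rate between patients, or clustering of events, are what matter.

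Nearby wording does not add weight. Calling counts continuous, and the abstract's compressed version, are clerical. The Outcomes section describes patient-reported measures "which include data on health system utilization using composites of items from" surveys, while Data collection says "Healthcare utilization and cost outcome measures will be obtained from health administrative data". Which source supplies the visit counts deserves a clarification of its own, but the two may be complementary and neither bears on the variance.

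**Conclusion.** The point holds in conditional form. The article assigns three secondary count outcomes to Poisson regression with no stated allowance for overdispersion, in a population where overdispersion is likely though not documented. If model-based standard errors are used, the nominal 5% error would be about 11% to 38% for φ between 1.5 and 5, and about 5% to 7% for φ between 1.0 and 1.2. The formula is firm and confirmed by simulation; the values of φ are assumptions.

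Severity is moderate. Only secondary outcomes are touched, the article states no significance rule for them, and the HbA1c analysis with its power of 0.997 stands.

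**What to change.** In the Data analysis section, state that emergency department visits, physician visits and hypoglycaemic episodes will be analysed by Poisson regression with robust (sandwich) or quasi-likelihood variance, or by negative binomial regression, and fix which one before outcome data are seen. Call these outcomes counts there and in the abstract.

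The change takes a sentence or two and needs no new data. Intervals widen by about √φ where the counts are overdispersed, for example 1.22 times at φ = 1.5 and 2.24 times at φ = 5. Where φ is close to 1 they hardly change. Robust standard errors ran slightly above nominal in some settings (up to 6.0%), which is small beside the error they remove.
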